#### 2.5.2. Secondary Outcomes

Secondary outcomes can be grouped around: affectivity, personality traits, quality of life and interference, emotion regulation, aspects related to surgical complications, eating behaviors and body image, and satisfaction with and evaluation of the treatment received.

To assess affectivity, the Positive and Negative Affect Scale (PANAS [53,54]) will be administered to evaluate positive and negative affect. Personality will be measured with the NEO Five-Factor Inventory (NEO-FFI [55]), which offers a rapid and general measure of the Big Five personality traits of which we will only assess Neuroticism and Extraversion. The Quality of Life Index (QLI [56]) will be used to evaluate several aspects related to quality of life (i.e., physical disability, emotional well-being, self-care and independent functioning, occupational functioning, interpersonal functioning, social–emotional support, community and services support, personal fulfillment, spiritual fulfillment, and overall quality of life). EuroQol [57,58] is a generic instrument that will be used to measure health-related quality of life. It has five dimensions (mobility, personal care, daily activities, pain, and anxiety/depression), and a general state of health perceived through a visual analog scale. Similarly, the Maladjustment Inventory (MI [59]) will be used to evaluate the extent to which the subject’s current problems impact negatively on different areas of daily life, namely, work, social life, leisure time, relationship with the partner, family life, and overall adjustment in daily activities.

Regarding emotion regulation, it will be assessed using the Difficulties in Emotion Regulation Scale (DERS [60,61]), which presents five dysregulation dimensions: emotional lack of control, emotional rejection, life interference, lack of emotional attention, and emotional confusion. In addition, to assess the different emotion regulation skills that will be trained through the UP, we will use the Brief Experiential Avoidance Questionnaire (BEAQ [62,63]), which is a self-report questionnaire with 15 items that measure experiential avoidance; the Philadelphia Mindfulness Scale (PHLMS [64,65]), which is a 20-item questionnaire that assesses two mindfulness constructs: awareness and acceptance and the Emotion Regulation Questionnaire (ERQ [66,67]), which is a self-report questionnaire commonly used to assess two emotion-regulation strategies: cognitive reappraisal (six items) and expressive suppression (four items).

To assess surgical complications, the professional will be asked to refer the participant to the mental health unit a report describing the course of the operation and the recovery from it. Specific measures related to eating disorders will also be used, such as the Bulimic Investigatory Test (BITE [68,69]), which is a self-report questionnaire used to evaluate the presence and severity of bulimic symptomatology, and cognitive and emotional signs and symptoms associated with binge eating; the Body Satisfaction Questionnaire (BSQ [70,71]), which is a self-applied scale used to evaluate the fear of gaining weight, feelings of low self-esteem because of one’s appearance, the desire to lose weight, and body dissatisfaction, and Emotional Eating Scale (EES [72]), which is a 25-item self-report assessing a person’s tendency to cope with negative affect through eating. Participants’ weight will be checked monthly to calculate their body mass index (BMI).

Additionally, we created an ad hoc questionnaire to evaluate the participants’ evaluation of and satisfaction with the treatment received, the Satisfaction with Treatment Questionnaire (STQ). The Evaluation of the UP Components section consists of nine items that evaluate the extent to which the participants consider that the UP in general, and each of its components in particular, were useful to help them to regulate their emotions adaptively; the Satisfaction with Treatment section presents seven items that evaluate participants’ overall satisfaction with the treatment received. In both sections, higher scores show higher levels of positive evaluation and satisfaction. A total of 12 items will also be added to assess the participants’ opinion of the online evaluation through Qualtrics and of the Cisco Webex platform used to carry out the online evaluation. At the end of the questionnaire, six open-ended questions appear in which the participants can qualitatively express their opinion of different aspects of the treatment received and the delivery format.

All measures used in the study have been standardized in Spanish. Administration time is between 30 and 40 min for the MINI and approximately 90 min for the primary and secondary outcomes conjointly.

#### 2.5.3. Baseline Assessment

To facilitate the daily baseline assessment, we have summarized in one item the variable we want to evaluate, for example, the emotion regulation strategies. For this purpose, we have chosen the item with the greatest factor load for each variable [73]. Specifically, participants will answer a battery of 19 questions: six questions about the presence and intensity of specific emotions (e.g., happiness, sadness, anxiety); five questions to assess the five subscales of the Difficulties in Emotion Regulation Scale (DERS [60,61]), which are emotional lack of control, emotional rejection, life interference, lack of emotional attention, and emotional confusion (e.g., “During this day, to what extent have you paid attention to your feelings?”); two questions that refer to the two subscales of the Emotion Regulation Questionnaire (ERQ [66,67]), which are reappraisal and suppression (e.g.,” During this day, to what extent have you been able to control your emotions by changing the way you think about the situation you were in?”); two questions that refer to the two subscales of the Philadelphia Mindfulness Scale (PHLMS [64,65]), which are acceptance and awareness (e.g., “During this day, when your emotions have changed, to what extent have you been aware of it immediately?”); one question to assess experiential avoidance based on the Brief Experiential Avoidance Questionnaire (BEAQ [62,63]) (“During this day, would you say that one of your biggest goals has been to be free of any painful emotion?”); one question from the Emotional Eating Scale (EES [72]) regarding the impulse to eat as a consequence of having experienced an intense emotion (“During this day, to what extent have you felt the urge to eat as a result of experiencing intense emotions?”) and one last question from the Body Satisfaction Questionnaire (BSQ [70,71]), which asks about the extent to which the participant has been satisfied with their body image (“During this day, how satisfied have you been with your body image?”).

#### 2.5.4. Assessment during Treatment

The assessment during treatment battery involves continuing to fill in the same baseline questions once a week. In addition, before starting each online session, participants will be asked to fill in an emotional scale to assess its presence, intensity, and interference during the last week. Participants can choose the emotion or emotions that should be assessed. The UP offers four different emotional rating scales: The Overall Anxiety and Depression Severity and Impairment Scales (OASIS; ODSIS [74,75,76]), Other Emotions Severity and Impairment Scale (e.g., guilt, shame, or anger) (OESIS [77]), and a Positive Emotion Severity and Impairment Scale (e.g., happiness) (PESIS [77]; Supplementary Materials). All of them are used in the UP to help patients to continuously monitor the scores throughout the sessions and their progress over the treatment.

### 2.6. Data Analysis

The analyses will be carried out with the statistical package IBM SPSS Statistics version 22.0 for Windows [78]. First, the sociodemographic characteristics of the sample will be analyzed with descriptive statistics, calculating the mean and standard deviation of the scores in the different questionnaires administered. Next, a missing-value analysis and the Little Missing Completely At Random (MCAR) test will be performed to determine whether or not the distribution of missing values is random, and therefore whether the last observation made (LOCF) can be used. Internal consistency will be explored using Cronbach’s alpha.

As the sample size is expected to be less than 50, the normal distribution of the variables will be verified with the Shapiro–Wilk normality test. Depending on the result of this test, parametric or non-parametric repeated measures analysis will be carried out to verify whether or not the differences in the scores of the variables measured at different times are statistically significant. In case the variables follow a normal distribution, parametric repeated measures analysis will be carried out, specifically the Multivariate Analysis of Variance (ANOVA), and in case the variables do not follow a normal distribution, non-parametric repeated measures analysis will be carried out, specifically the Friedman test. If the repeated measures analysis show statistically significant differences between the evaluation time points, post-hoc comparisons will be carried out to correct the level of significance to avoid increasing the type I error. Thus, regarding adjustment for multiple comparisons, the Bonferroni correction will be carried out in case of having performed parametric analysis, and the Wilcoxon signed rank test in case of having performed non-parametric analysis in the comparison of means. More detailed information on this has been added in the data analysis section, explaining step by step which statistical analyzes will be carried out.

Finally, the Reliable Change Index (RCI), which assesses the clinically significant change obtained to determine in which variables the scores have approached those of the normative sample, will be calculated. A clinically significant change will be considered if the RCI score obtained is equal to or greater than 1.96 [79].

Another aspect that we consider important to analyze is how the participants change their scores in each of the variables evaluated based on the content addressed each module. For this purpose, a visual analysis of the changes in the scores will be carried out, to see how the slopes change in the different phases of the study (evaluation and treatment), and in the different modules within the treatment. This visual analysis has been used in previous studies [21]. To carry out this visual analysis, the data from 19 questions that the participants will fill in weekly will be used.

Attendance at sessions will also be recorded to calculate the attendance rate, which will be used as an indicator of viability and acceptance of treatment by users. For the same purpose, quantitative and qualitative analyses will be carried out. At the quantitative level, the participants’ evaluation of and satisfaction with the treatment received will be evaluated using an ad hoc designed questionnaire (see “Measures” section). Qualitatively, participants will be asked to answer six main questions about treatment, and their answers will be analyzed by selecting and classifying the information through a segmentation process, identifying key themes and categories of analysis [80].

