The specific objectives pursued are: to evaluate adherence to treatment and clinical improvement in the primary and secondary measures after applying the UP and to study its long term clinical usefulness until two years after the intervention. Thus, the main hypotheses proposed for this study are: (1) statistically significant differences (reliable change index; RCI) will be obtained between the scores obtained at the pre-treatment, baseline, and post-treatment on the primary and secondary measures; (2) the improvements obtained after the application of the UP will be maintained in the long term (follow-ups of up to two years); (3) participants in the pilot study will report high adherence rates and high satisfaction scores regarding the treatment delivery format and its components.

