### 2.1. Sample and Recruitment

The study recruitment will start in September 2020 until December 2024. The study will be conducted in a public mental health center in Spain (Mental Health Unit of the Regional Hospital of Vinaròs, Castellón). Participants will be people over 18 years of age who have anxious or depressive symptoms, or at least one diagnosis of EDs according to Diagnostic and Statistical Manual of Mental Disorders five edition criteria [39] and who have been selected for a subsequent BS.

To calculate the sample size, we drew on a study that proposed stepwise rules of thumb for pilot studies based on the target effect size and the size of the future trial [40]. Previous works that study the efficacy of CBT procedures either in person or online have shown large variations in effect sizes, obtaining mainly medium to large effect sizes [41,42]. Taking these data into account, and expecting a 90% powered main trial and assuming a sample loss of 35% [43] we established a sample size of 20 participants per experimental condition for the present study, that is, a total sample of 60 participants.

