### 2.3. Eligibility Criteria

The inclusion criteria for participation in the project will be: (1) being over 18 years of age; (2) being a BS candidate; (3) presenting anxious or depressive symptomatology (moderate scores on the Beck Depression Inventory-II [46,47] and/or Beck Anxiety Inventory [48,49]) or meeting the criteria for at least one ED (anxiety, mood, and related disorders) on the International Neuropsychiatric Interview (MINI; [50]); (4) speaking Spanish or Catalan fluently; (5) committing to attend the sessions; (6) understanding and accepting the contents of the informed consent, expressed by signing it; (7) having Internet to fulfill the protocol assessments and to participate in the online intervention and (8) agreeing to maintain the prescribed medication (including dosage) if any, during the evaluation period and treatment. If medication stability is not possible, the participant’s data will be treated separately in the analyses.

The protocol also includes one exclusion criteria that may interfere: (1) having a severe condition that would require being prioritized for treatment, so that an interaction between the two interventions cannot be ruled out. These include a severe mental disorder (bipolar disorder, personality disorder, schizophrenia, or an organic mental disorder), suicide risk at the time of assessment, or substance use in the last three months (excluding cannabis, coffee, and/or nicotine).

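### Little's MCAR test cannot license LOCF: LOCF needs a flat course after dropout, which MCAR does not imply and which the two-year maintenance hypothesis sets out to test

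*Protocol article*

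**What the plan says.** Section 2.6 (Data Analysis) plans a missing-value analysis and Little's test "to determine whether or not the distribution of missing values is random, and therefore whether the last observation made (LOCF) can be used". It names no other way of handling missing scores. The scores then go into a repeated-measures ANOVA or a Friedman test, followed by individual RCIs with a threshold of 1.96.

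Section 2.1 plans "a total sample of 60 participants", "assuming a sample loss of 35" per cent, and does not say when the loss is expected. Among the main hypotheses in the Introduction, the second is that "the improvements obtained after the application of the UP will be maintained in the long term", with follow-up to two years. Table 4 judges this at the individual level by RCI. Section 2.2 places the 3- and 6-month follow-ups before surgery and all later ones after it.

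**The concern.** The rule confuses two different assumptions. MCAR says that the reason a score is missing is unrelated to the scores. LOCF assumes that the missing score equals the last one seen. Data can be perfectly MCAR while every participant is changing, and LOCF is then biased.

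The document gives reasons to doubt a flat course. The Introduction describes psychological gains after surgery as limited to the first months, with symptoms later returning. The Discussion places the return of problems at around a year and a half to two years. Surgery itself falls inside the follow-up period, and BMI is a primary outcome.

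The maintenance hypothesis is at stake. If a participant gives no score after post-treatment, LOCF sets the post-to-follow-up change and its RCI to exactly 0 and makes the pre-to-follow-up RCI equal to the pre-to-post RCI. Maintenance is then imputed, not observed. Repeated-measures ANOVA and Friedman both need complete rows over as many as ten assessments, so the filling rule has a large say in the result.

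**Working it through.** **Inputs from the Protocol article**
- N = 60, 20 per baseline condition; loss d = 0.35, timing not given (section 2.1).
- Follow-ups every three months for 24 months: 24 / 3 = 8. With pre- and post-treatment this makes ten full assessments (section 2.2, Table 3).
- Effect size: only "obtaining mainly medium to large effect sizes", with no number (section 2.1).

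**Assumed for illustration, not in the document:** SD 1 at each visit, within-person correlation 0.6, pre-to-post gain 0.8 SD, two-sided 5% level, and MCAR truly holding.

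**The plan's own figure.** 60 × (1 − 0.35) = 39 and 39 / 0.65 = 60; per condition, 20 × 0.65 = 13. The attrition arithmetic is consistent, with 60 − 39 = 21 lost. The figure of 20 per condition cannot be re-derived. It rests on a cited rule of thumb and "expecting a 90% powered main trial", so the power belongs to a later trial.

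**Symptom scales, loss after post-treatment.** Under full relapse, the share of the gain falsely retained is d × (1 − f), where f is the mean share of the relapse already visible at the last score.
- All loss right after post-treatment: f = 0, so 0.35 × 1 = 35%, and 0.35 × 0.8 = 0.28 SD.
- Loss spread evenly over follow-up with linear relapse: the last score is equally likely to be post-treatment or any of follow-ups 1 to 7. Then f = (0 + 1 + … + 7) / (8 × 8) = 28 / 64 = 0.4375, the share is 0.35 × 0.5625 = 0.197 (about 20%), and 0.197 × 0.8 = 0.16 SD.

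Simulation with 4,000 runs per scenario, for the change from post-treatment to 24 months:

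| True relapse (SD) | Loss | LOCF estimate (SD) | Coverage of 95% interval |
|---|---|---|---|
| 0.40 | right after post | 0.26 | 68% |
| 0.40 | spread over follow-up | 0.32 | 90% |
| 0.80 | right after post | 0.52 | 27% |
| 0.80 | spread over follow-up | 0.64 | 74% |

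The observed-data (completer) analysis gave 0.40 and 0.80, with about 95% coverage. Under full relapse the LOCF interval for the pre-to-24-month change excluded the true zero in about 60% of runs (loss right after post) or 26% (spread).

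**Symptom scales, loss during treatment.** Table 3 schedules these scales at pre-treatment, post-treatment and follow-up only, so the score carried forward is the pre-treatment one. With a share q lost then, and the gain otherwise holding, the reported gain is (1 − q) × true gain. For q = 0.35: 0.65 × 0.8 = 0.52 SD, 35% too small. For q = 0.175 (half the loss): 0.825 × 0.8 = 0.66 SD, 17.5% too small.

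**BMI.** The same formula applies to the surgical fall, with q the share lost before surgery but then operated on. For q = 0.10, 0.20 and 0.35 the fall is understated by 10%, 20% and 35%. No assumed size of the fall is needed.

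**Standard errors.** The variance of a change score is 2 × (1 − 0.6) = 0.8, so the observed-data SE is √(0.8 / 39) = 0.143.
- Post to follow-up, no mean change, loss right after post: √(0.65 × 0.8 / 60) = 0.093; ratio 0.65.
- The same, loss spread: only one in eight of those lost has an imputed change of exactly 0. The variance is 0.8 × (0.65 + 0.35 × 7/8) = 0.765, and √(0.765 / 60) = 0.113; ratio 0.79.
- Pre to follow-up, full relapse, loss right after post: mixing the two groups adds 0.35 × 0.65 × 0.8² = 0.146, and √(0.946 / 60) = 0.126; ratio 0.88.

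**The test as gatekeeper.** As a proxy for Little's test, a t-test of the baseline score (21 lost against 39 kept) detects a difference of 0.3 SD with 19% power, 0.5 SD with 44% and 0.8 SD with 83%. A non-significant result is weak evidence of MCAR. The plan states no threshold; non-significance is the natural reading.

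**The case against.** The strongest defence is that LOCF can be harmless. With a truly flat course and loss only after post-treatment, the simulation found it unbiased, with about 95% coverage. The post-to-follow-up test kept its 5% error rate, and at a true relapse of 0.40 SD it had about the same power as the completer test (77% each, loss right after post). That stands. The harm lies in the estimates, the intervals, the pre-to-follow-up comparison and the individual RCIs, and it appears when the course is not flat or when loss occurs during treatment. The study is also a pilot that asks for cautious interpretation. This tempers the consequence but does not repair the inference. A separate analysis plan might add detail, but the rule is stated in the article and is wrong as stated.

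Three stronger readings are tempting, and the document does not support them.
- A reader might infer that LOCF always favours the intervention. It does not: loss during treatment, and loss before surgery for BMI, bias the other way.
- A reader might see a contradiction between LOCF, which keeps all 60, and "As the sample size is expected to be less than 50". That phrase only explains the choice of the Shapiro–Wilk test. It agrees with 60 × 0.65 = 39, and LOCF is conditional in the plan.
- A reader might infer from section 2.3 that participants whose medication changes are removed. The text says their "data will be treated separately in the analyses", which also fits separate reporting or stratification. Nothing in the document says that they change medication because they worsen.

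**Conclusion.** The point holds and should be fixed before analysis. Passing Little's test does not make LOCF valid, and with about 21 of 60 lost the test is itself weak.

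The size depends on the timing of loss, so it is a range in both directions. Under full relapse, 20% to 35% of the gain is falsely retained when loss comes after post-treatment. The gain is understated by up to 35% when loss comes during treatment, and the fall in BMI by up to 35% when loss comes before surgery. Standard errors are about 0.65 to 0.79 of the observed-data value for post-to-follow-up change with no mean change. The ratio is about 0.88 for pre-to-follow-up change under full relapse with loss right after post-treatment.

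The percentages rest on the plan's 35% loss and the stated timings, and the 20% also on linear relapse. The standard errors and coverage also rest on the assumed correlation of 0.6 and, where relevant, the gain of 0.8 SD. The power figures come from a proxy, not from the multivariate test.

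**What to change.** Delete the sentence that makes LOCF depend on Little's test, and keep the test as description only. Then:
- Continuous outcomes: fit a likelihood-based mixed model (SPSS MIXED) to all observed scores, with time as a categorical effect, valid under MAR. Prespecify a parsimonious covariance structure, because an unstructured one over ten assessments has 10 × 11 / 2 = 55 parameters for about 39 completers.
- MINI diagnosis: use the corresponding binary repeated-measures model.
- RCI: compute it from observed scores only, and report the number missing at each visit beside it.
- Sensitivity analysis: set lost participants back to their pre-treatment score. For symptom scales this is the relapse scenario. For BMI after surgery, read it only as an extreme bound.

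The cost is analysis work: no new data, participants or software. It does replace the ANOVA/Friedman scheme, and intervals may widen.

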The baseline and psychological intervention will be conducted between the period of acceptance for BS and the BS implementation, that last approximately one year in public health settings. The intervention will be carried out in an online group format through the Cisco Webex platform. The UP will be applied in twelve weekly 2-h online group sessions. To comply with the experimental design of the multiple baseline, when each participant completes the baseline evaluation, they will receive the first online session in individual format (to receive the first session in stages), then they will continue with the second session and the rest of the treatment in group format. The content of each session is shown in Table 2. Participants will receive the therapy support manual [11]. The online group will consist of five to eight participants, one therapist ([name]), and one co-therapist ([name]). For ethical reasons, if any of the patients feel uncomfortable during the study with the online group format, they may leave the group and receive individual onsite attention (treatment as usual). In this case, the content and estimated number of sessions will be the same, although the frequency will be stipulated by the mental health unit depending on its possibilities.

The study plans to conduct a follow-up assessment every three months until two years after treatment completion. All follow-ups will be conducted online. Considering the time interval of the baseline, the psychological intervention and the BS procedure, the two first follow-ups (three and six months after intervention) will be conducted before BS, and the rest will be conducted after BS. In addition, at the baseline and during treatment, the participants must fill out an online survey made up of 14 questions that will ask about the intensity of the emotions of happiness, sadness, anxiety, other emotions, difficulties in emotion regulation, body image, and emotional eating. Through this weekly evaluation, we expect to observe how the participants evolve in the different variables throughout the different treatment modules.

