**Clinical Usefulness of the UP for Bariatric Surgery Candidates**
**Group Results:**
- Depending on the characteristics of the sample obtained (we will check if the parametric assumptions are met), the results of the parametric/non-parametric tests that allow comparing the group scores between the different time points are expected to show statistically significant differences in the desired direction.

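### If carrying values forward is ruled out, the named group tests drop participants who have both pre- and post-treatment scores but miss a later follow-up entered in the same test

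*Protocol article*

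**What the plan says.** - **Sample size.** Section 2.1 of the protocol article states: "we established a sample size of 20 participants per experimental condition for the present study, that is, a total sample of 60 participants". The same sentence gives as its basis "assuming a sample loss of 35" per cent, and "expecting a 90% powered main trial", which is the power of a future trial and not of this pilot.
- **Schedule.** Section 2.2 states: "The study plans to conduct a follow-up assessment every three months until two years after treatment completion". That makes eight follow-ups. Table 3 collects most questionnaires at pre-treatment, post-treatment and the follow-ups, so up to ten occasions per scale.
- **Missing values.** Section 2.6 plans a missing-value analysis and Little's MCAR test, whose result decides whether last observation carried forward (LOCF) can be used. No other handling is named.
- **Group tests.** Section 2.6 opens its testing paragraph with "As the sample size is expected to be less than 50", as the reason for using Shapiro-Wilk. It then names repeated-measures analysis of variance (labelled multivariate) for normal data and Friedman otherwise, "to verify whether or not the differences in the scores of the variables measured at different times are statistically significant". Post-hoc comparisons follow only a significant overall result: Bonferroni-corrected on the parametric route, Wilcoxon signed rank on the other.
- **Expected group results.** Table 4 describes tests "comparing the group scores between the different time points". Neither place lists which occasions enter one test.
- **Individual results.** The first hypothesis (end of section 1) and Table 4 use the Reliable Change Index (RCI) for change up to post-treatment.

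**The concern.** Repeated-measures analysis of variance and Friedman both work on complete rows, so a participant who lacks one of the occasions entered leaves the whole test. The plan's only protection against this is LOCF, and by the plan's own rule LOCF falls away when missingness is found not to be random. The complete-row tests are then all that is named, in the very situation where the participants with complete rows cannot be assumed to represent the rest.

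If the two years of follow-up share a test with pre and post, attendance long after treatment decides whose pre-post change counts in the group analysis. On the parametric route this reaches both the overall test and the Bonferroni pre-post comparison. On the non-parametric route it reaches the Friedman test, which decides whether any pairwise comparison is made. At stake are discarded data, lost precision, and a group result that describes those who kept attending.

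**Working it through.** **Inputs from the documents.** 60 participants and 35% loss (section 2.1); pre, post and eight follow-ups, so ten occasions and nine intervals (section 2.2, Table 3).

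**Assumptions, not in the documents.** All ten occasions enter one test; LOCF is not used; the 35% is reached by the last follow-up; loss is monotone (nobody returns after a missed visit). The timing of loss is not stated, so it is varied.

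**1. The plan's own figure.** 60 × (1 − 0.35) = 39. This is below 50, so the remark in section 2.6 agrees with section 2.1. Per condition, 20 × 0.65 = 13.

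**2. Complete rows.** Under monotone loss, only those still present at two years have all ten values: 39.

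**3. Participants with both pre and post, and pairs lost.** Pairs lost = (number with both) − 39.

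| Timing of the 35% loss | Both pre and post | Complete rows | Usable pairs lost |
|---|---|---|---|
| All after post | 60 | 39 | 21 |
| Constant per interval | 60 × 0.65^(1/9) = 60 × 0.953 ≈ 57 | 39 | about 18 |
| 10% of participants lost by post | 60 × 0.90 = 54 | 39 | 15 |
| 20% of participants lost by post | 60 × 0.80 = 48 | 39 | 9 |
| All before post | 39 | 39 | 0 |

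**4. With LOCF.** Everyone with both values has the later ones filled in, so no pre-post pair is lost. The loss arises only when LOCF is ruled out.

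**5. What the loss means for a pre-post comparison.** Paired t-test, two-sided 5%, noncentral t with noncentrality 0.5 × √n, at an assumed standardised change of 0.5:
- n = 39: power 0.86
- n = 57: power 0.96

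These are for a single unadjusted comparison. The Bonferroni correction would lower both.

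**6. Sensitivity to scattered missed visits.** The documents give no rate for these. If the 39 also missed each of the eight follow-ups at random with probability 5% or 10%, complete rows would be 39 × 0.95^8 ≈ 26 or 39 × 0.90^8 ≈ 17. This shows only the direction; the conclusion does not rest on it.

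**7. Which planned results are touched.**

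| Planned result | Values needed | Affected? |
|---|---|---|
| Overall repeated-measures test | Every occasion entered | Yes |
| Bonferroni pre-post comparison based on it | Every occasion entered | Yes |
| Friedman test | Every occasion entered | Yes |
| Wilcoxon pre-post comparison | The two values | Only through the Friedman result that must come first |
| Individual RCI | The person's two scores | No |

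**The case against.** The strongest reply is that the problem is conditional. LOCF may be permitted, and then no pair is lost. The article does not list the occasions per test, and it states change up to post-treatment and long-term maintenance as separate hypotheses, so separate tests are possible. On the non-parametric route the pre-post comparison itself needs only two values. All of this stands and limits the point. It does not remove it: the document names no group test other than the complete-row ones for the case where LOCF is ruled out, and its wording on time points reads most naturally as one test across all of them.

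It can also be said that an article leaves analysis sets and fallback rules to a fuller plan. That is fair for what is merely unstated. The choice of tests and the rule for LOCF are stated, however, and the loss follows from them.

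Three stronger readings are tempting, and the documents do not support them:

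- **That fewer than 50 contradicts 60.** A reader might set "As the sample size is expected to be less than 50" against "that is, a total sample of 60 participants". The first follows from the second after 35% loss, and it only justifies a normality test. It does not define an analysis set.
- **That the first hypothesis would be judged on two-year attenders.** That hypothesis is framed on the RCI, which is computed per person and loses nobody through a missed follow-up.
- **That only a minority would be analysed.** On the plan's own figure 39 of 60, or 65%, have complete rows. A minority appears only with an added rate of scattered missed visits that the document does not give.

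**Conclusion.** The point holds in conditional form, as an improvement worth making. Where LOCF is ruled out and the follow-ups share a test with pre and post, the named group tests lose between 0 and 21 usable pre-post pairs out of 60. The loss is about 18 if the 35% accrues evenly over the nine intervals, and power for a standardised change of 0.5 is then about 0.86 instead of 0.96. The range rests on monotone loss with unknown timing, and the power figures on an assumed effect.

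The cost in power is moderate, and this pilot claims no power of its own. The more important weakness is that the complete-row analysis applies exactly where the plan's own check has found missingness not to be random. The size of any resulting bias cannot be derived from the documents.

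**What to change.** In section 2.6, replace the complete-row group tests and the LOCF rule that depends on Little's test with one linear mixed model for repeated measures per scale (SPSS MIXED, REML, time as a categorical factor). Fit it to all observed values from every participant with a pre-treatment score, and take the pre-post and follow-up contrasts from that model. As a minimum, test pre versus post in everyone who has both values, separately from the follow-up occasions, and list the occasions that enter each test.

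The remark about fewer than 50 need not be corrected.

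The cost is a rewording of one section and a different procedure in the same software, with no new data or participants. The downside is that a covariance structure must be chosen for up to ten occasions with at most 60 participants. An unstructured matrix has 10 × 11 / 2 = 55 parameters, so a simpler structure would probably have to be specified in advance. The model also relies on missingness being explained by the observed scores, which is weaker than missingness being completely random but is still an assumption.
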